1.1 Study Identification

Status: Approved

**4.0**    **\* Is the proposed research:**  
Funded (Grant, subgrant, contract, internal funds, donation or some other source of funding)

1.2 Additional Approval

Status: Approved

## 1.2 Additional Approval

- 1.0** *\* Departmental Review: Please note only ONE Department Review is required. Please ensure that this section reflects only the PRIMARY Department of the study PI.*

RM Physical Therapy

- 2.0** **Internal Review** (If the Principal Investigator is in the Department of Medicine complete the Department of Medicine Request for Internal Approval form and upload it to the "Documentation" section of this application under item 11.0 "Other Documents". Note that all fields in the form are required. The form is available at [here](#)):

ID: Pro00043397

Pro00043397

1.3 Funding Information

Status: Approved

## 1.3 Study Funding Information

- 1.0** *\* Type of Funding:*  
Grant (external)

- 2.0 \* Indicate which office administers your award. (It is the PI's responsibility to provide ethics approval notification to any office other than the ones listed below)**  
University of Alberta - Research Services Office (RSO)

**To connect your ethics application with your funding: provide all identifying information about the study funding – multiple rows allowed. For Project ID, enter a Funding ID provided by RSO/PeopleSoft Project ID (for example, RES0005638, G018903401, C19900137, etc). Enter the corresponding title for each Project ID.**

| Project ID                      | Title | Grant Status | Sponsor | Project Start Date | Project End Date | Purpose | Other Information                                      |
|---------------------------------|-------|--------------|---------|--------------------|------------------|---------|--------------------------------------------------------|
| View RES0050918 |       |              |         |                    |                  |         |                                                        |
| View RES0004194 |       |              |         |                    |                  |         |                                                        |
| View RES0017547 |       |              |         |                    |                  |         | SickKids
New
Investigator
Grant NI14-
018R |

### 3.0 \* Funding Source

#### 3.1 Select all sources of funding from the list below:

|                                  |       |
|----------------------------------|-------|
| Glenrose Rehabilitation Hospital | GRH   |
| Scoliosis Research Society       | SCOL  |
| Sick Kids Foundation             | SICKK |

**3.2 If your source of funding is not available in the list above, click "Add" below and write the Sponsor/Agency name(s) in the free text box that pops up. (Note: You may reflect multiple sources of funding by continuing to click "Add" to add each additional source of funding).**

There are no items to display

- 4.0 \* Indicate if this research sponsored or monitored by any of the following:**  
Not applicable

***The researcher is responsible for ensuring that the study complies with the applicable US regulations. The REB must also comply with US Regulations.***

ID: Pro00043397

Pro00043397

1.4 Conflict of Interest

Status: Approved

## 1.4 Conflict of Interest

- 1.0 \* Are any of the investigators or their immediate family receiving any personal remuneration (including investigator payments and recruitment incentives but excluding trainee remuneration or graduate student stipends) from the funding of this study that is not accounted for in the study budget?
- ☐ Yes ☒ No
- 2.0 \* Do any of investigators or their immediate family have any proprietary interests in the product under study or the outcome of the research including patents, trademarks, copyrights, and licensing agreements?
- ☐ Yes ☒ No
- 3.0 \* Is there any compensation for this study that is affected by the study outcome?
- ☐ Yes ☒ No
- 4.0 \* Do any of the investigators or their immediate family have equity interest in the sponsoring company? (This does not include Mutual Funds)
- ☐ Yes ☒ No
- 5.0 \* Do any of the investigators or their immediate family receive payments of other sorts, from this sponsor (i.e. grants, compensation in the form of equipment or supplies, retainers for ongoing consultation and honoraria)?
- ☐ Yes ☒ No
- 6.0 \* Are any of the investigators or their immediate family, members of the sponsor's Board of Directors, Scientific Advisory Panel or

comparable body?

☐ Yes ☒ No

**7.0** \* Do you have any other relationship, financial or non-financial, that, if not disclosed, could be construed as a conflict of interest?

☐ Yes ☒ No

Please explain if the answer to any of the above questions is Yes:

### **Important**

*If you answered YES to any of the questions above, you may be asked for more information.*

ID: Pro00043397

Pro00043397

Status: Approved

**List all health care research sites/locations:**

**EDMONTON SITE**

Recruitment will primarily be done via the Edmonton Scoliosis Clinic at the Glenrose Rehabilitation Hospital and Stollery Hospital (Radiographs and Quality of Life questionnaires will be extracted from the clinical databases). In addition, the primary care physicians will also be involved in recruitment should they agree to.

Surface topography scans will be recorded at the Clinical Sciences Building, room 6-107 Scoliosis Surface Topography Lab, affiliated with the Stollery's Edmonton Scoliosis Clinic.

Montréal.

In Montréal the sites above are not linked with AHS or Covenant Health.

**3.0**

**Multi-Institution Review**

- \* 3.1 Has this study already received approval from another REB?**

☐ Yes ☒ No

**4.0**

**If this application is closely linked to research previously approved by one of the University of Alberta REBs or has already received ethics approval from an external ethics review board(s), provide the study number, REB name or other identifying information. Attach any external REB application and approval letter in the Documentation Section – Other Documents.**

The present study is an extension to multiple site of the pilot SETS study approved by HREB as Pro00011552 with the exception that we do not plan to collect blood samples at this point in the multicenter study.

- The surface topography assessment protocol has been used in the study: "Full Torso Surface Topography for Scoliosis" (PRO00006268) and in the study: "360 Degrees Surface Topography Parameters (Norms)" (PRO00003600)
- The use of SRS-22 Questionnaire was approved in all of the above mentioned studies.
- The physical assessment has been approved in the PRO00006957 and

in the PRO00003600 studies.

- The radiograph analyses have been approved in the PRO00006268 study.

ID: Pro00043397

Pro00043397

2.1 Study Objectives and Design

Status: Approved

**2.0 \* Provide a full description of your research proposal outlining the following:**

- **Purpose**
- **Hypothesis**
- **Justification**
- **Objectives**
- **Research Method/Procedures**
- **Plan for Data Analysis**

**Schroth Exercise Trial for Scoliosis**

**Background**

Adolescent Idiopathic Scoliosis (AIS), a 3D spinal deformity, is the most common orthopedic condition in adolescents requiring elective surgery and affects mostly females. In mild scoliosis from  $10^{\circ}$  to  $25^{\circ}$  the ratio is 4:1, in moderate AIS from  $25^{\circ}$  to  $50^{\circ}$  the ratio is 7:1, while in severe AIS  $>50^{\circ}$  the ratio is 10:1. Scoliosis reduces quality-of-life, often results in pain, poor function and self-image.

Usually, curves between  $25^{\circ}$ - $45^{\circ}$  are prescribed a brace and curves over  $45^{\circ}$  are treated surgically. Smaller curves are not treated. The

Schroth method utilizes asymmetric 3D endurance, strength and breathing exercises aiming to correct posture and scoliotic curves. Schroth therapists provide support by skillful resistances, auxiliary handholds, and specific verbal instructions and feedback from mirrors. Schroth exercises aim to restore proper physiological three-dimensional alignment.

Schroth treatment has proven effective in improving strength, posture, slowing progression and improving Cobb angle in many cohort studies. However, these results have not yet been tested in RCTs.

### **Objectives**

To conduct a RCT on the effect of Schroth exercises for AIS compared to the current treatment standard (observation or bracing prescribed as per SRS guidelines). Specific objectives are to compare the effects of 6-month of Schroth exercises added to standard care to standard care alone on curve severity measured using the Cobb angle, and on secondary outcomes including quality-of-life, spinal appearance, objective posture and spinal muscle endurance measurements. We will also compare the effect of 6 months of Schroth therapy offered to control participants after completing 6 months in the standard care group and determine if effects can be maintained until maturity once supervision is terminated.

### **Methods**

#### Subjects

Female patients with AIS, JIS, or syringomyelia without chiari (n=208) will be recruited in Edmonton, Calgary and Montréal. Inclusion criteria are: (1) curves 10°-45°, (2) age 10-16 (3) All Schroth curve types (3c, 3cp, 4c and 4cp), (4) treated with or without brace (5) living within 1 hour of the study site and (6) with Risser sign less than or equal to 3. Those planning or post-surgery will be excluded.

#### Procedures

At routine scoliosis clinic visits a nurse will determine eligibility and randomize participants to the observation (control) or the Schroth

exercise group. Outcomes will be measured at baseline, 3 and 6 months. Primary outcomes include baseline and 6-month radiographic curve measurements and SRS-22 questionnaire. Secondary outcomes will include postural measures (Surface Topography), Global Rating of Change (GRC), Self-efficacy questionnaire, pain, and back muscle endurance. Predictors of success will be collected at baseline.

Controls will receive the current standard of treatment for 6 months (Observation or brace prescribed as per SRS guidelines). Patients treated with Schroth exercises will participate weekly in supervised Schroth exercises and complete a daily home program for 6 months. The baseline and 6-month exam will be completed within 2 weeks of a scoliosis clinic visit with a follow-up at 3 months. After 6 months, controls will crossover to the treatment group. After 12 months and for every scoliosis visit afterwards until discharge, we will also extract the radiograph and SRS-22 questionnaire from the Edmonton Scoliosis records

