#### Questionnaires:

*Demographic/History-* Socio-demographics, symptoms history and modifying factors will be self-reported.

*Pain rating and diagram-* A numeric scale from 0 (no pain) to 10 (worst imaginable pain) will assess current, best, worst intensity in the last 24 hours. A diagram will assess location of symptoms.

*Scoliosis-Research-Society questionnaire (SRS-22r)-* The SRS-22r assesses quality-of-life within 5 domains: function, pain, self-image, mental health (5 questions each), and satisfaction (2 questions).

*3D Physical activity recall (3DPAR)*- quantifies habitual physical activity chosen among 55 activities listed, and their intensities for blocks of 30-min over 3 days. The 3DPAR score is determined using the metabolic equivalent (MET) levels.

*Spinal Appearance Questionnaire*- includes 21 items pertaining to the severity of the deformity within 9 domains (Trunk shift, Waist, Kyphosis, Prominence, Chest, Shoulders, General and Curve) .

*Self-efficacy* – measures self-efficacy for overcoming barriers to physical activity using 8 items rated from 1 (Disagree a lot) to 5 (Agree a lot).

*Global Rating of Change (GRC)*- A 15-point GRC ranging from –7 (very great deal worse) to +7 (very great deal better) will be used.

Physical Exam(Appendix E): An physiotherapist blind to groupings will assess curve type and hip range-of-motion in flexion, extension, internal rotation, the straight-leg-raise and FABERE tests. Sorensen's test will assess back extensor muscle endurance. Lumbar (inclinometers at L5/S1 and T12/L1) and thoracic (C7/T1 and T12/L1) spinal range-of-motion will be recorded: lumbar flexion, extension and side flexions. Scoliometer will record asymmetry during the Adam bending test.

Radiographs- Standing postero-anterior radiographs in a positioning frame at baseline, 6 and 12 months and from every scoliosis clinic visits until discharge will be used to measure the Cobb angle, rotations, apex translation. An experienced evaluator blind to group assignment will extract measures.

Surface topography(ST) – An experienced evaluator will operate four scanners and use a positioning frame to scan torso shape. The following ST parameters will be extracted by digitizing 15 points on de-identified scans (blinding): cosmetic score, shoulder angle, scapula angle, waist asymmetry, trunk rotation, kyphotic and lumbar indices.

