## **Analyses:**

Intention to treat (by carrying forward last known value) linear mixedmodel analyses will be used to assess differences in group changes from baseline, to 3 and 6-month while adjusting for covariates. Separate analyses will be conducted for each outcome. To screen for variables associated with each of the outcomes variables, we will use univariate linear mixed models and include all relevant covariates (age, time since menarche, apex levels, physical activity, self-efficacy, and bracing compliance may have associations with risk of progression). Multiple linear mixed models will be tested including covariables found significant at  $P=0.20$  in the univariate analysis, and after screening for multicollinearity. Results will be presented as effect sizes with confidence intervals and one-sided P-values. Statistical analyses will be performed using SAS version 9.1.

For subjects initially in the control group later completing 6 months of exercises, intention to treat linear mixed-model analyses will be used to assess differences between the two periods (standard care vs standard care + Schroth) in changes from baseline, to 3 and 6-month, while adjusting for covariates. Screening for covariates will be done as described above. In this model, treatment period is a dependent factor.

To determine if exercises effects are maintained at 12 months and discharge exams, linear mixed- model analyses will also be used to quantify the effect sizes corresponding to changes from 6 to 12 months and to discharge by combining data from all patients after participating in the exercise program.

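### Objectives and Procedures name different primary outcomes (Cobb angle alone, or curve measurements plus SRS-22), and the sample size covers only one primary test

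*Protocol*

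**What the plan says.** Protocol section 2.1, Objectives, compares exercise plus standard care with standard care by itself, "on curve severity measured using the Cobb angle, and on secondary outcomes including quality-of-life, spinal appearance, objective posture and spinal muscle endurance measurements". Cobb angle stands alone as the main outcome, and quality of life is secondary.

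Procedures, in the same section, states: "Primary outcomes include baseline and 6-month radiographic curve measurements and SRS-22 questionnaire". Its next sentence reads: "Secondary outcomes will include postural measures (Surface Topography), Global Rating of Change (GRC), Self-efficacy questionnaire, pain, and back muscle endurance". SRS-22 is absent from that secondary list, so its place among the primaries is not offset there.

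The Questionnaires part of section 2.1 describes the SRS-22r as the quality-of-life measure, with five domains. Its radiograph paragraph says the films "will be used to measure the Cobb angle, rotations, apex translation", read by an evaluator blind to group. Neither paragraph says which radiographic measure or which SRS-22 score is primary.

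On testing, the Analyses part says "Separate analyses will be conducted for each outcome" and "Results will be presented as effect sizes with confidence intervals and one-sided P-values". It gives no significance level. The level appears in section 4.2, item 5.0 (sample size): 129 per group, effect size 0.31, 80% power, a one-sided test and alpha 0.05.

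**The concern.** A reader cannot tell from the protocol which result decides the trial. One section points to Cobb angle. The other points to at least two outcomes, one of them loosely specified. The choice could then be made after the results are known.

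The two candidates also differ in their exposure to bias. Radiographs are read blind. SRS-22 is completed by participants, at home according to section 2.9, and they know whether they were assigned to exercise. If the primary outcome is left open, the measure more open to expectation could become the basis of the main claim.

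There is a cost in error rate or power as well. If there are two primaries, either the false-positive rate exceeds the planned 5% (should one success be enough), or alpha must be divided and the planned power is lost.

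**Working it through.** **Inputs.** From section 4.2, item 5.0: effect size d = 0.31, one-sided alpha 0.05, power 80%, 129 per group (104 in this study plus 25 from the pilot). The count of two primaries, one curve measure and one SRS-22 score, is the minimum that Procedures implies. The correlations between outcomes are assumptions; the protocol gives none.

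**Step 1: reproduce the stated sample size.** n per group = 2(z₁₋α + z₁₋β)² / d².
- One test at one-sided 0.05: 2 × (1.645 + 0.842)² / 0.31² = 2 × 6.183 / 0.0961 = 128.7, so 129. This matches the protocol.
- Power at 129: Φ(0.31 / √(2/129) − 1.645) = Φ(2.490 − 1.645) = Φ(0.845) = 80.1%.

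The whole one-sided 0.05 is spent on one comparison, and nothing is reserved for a second primary.

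**Step 2: two primaries, either one sufficient, each at one-sided 0.05.**
- Independent: 1 − 0.95² = 9.75%.
- Positively correlated, by the bivariate normal distribution:

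| Assumed correlation | Chance of at least one false positive |
|---|---|
| 0.3 | 9.3% |
| 0.5 | 8.8% |
| 0.8 | 7.5% |

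**Step 3: two primaries with alpha split equally, one-sided 0.025 each.**
- Power per outcome at 129 and d = 0.31: Φ(2.490 − 1.960) = Φ(0.530) = 70.2%.
- Detectable effect at 80% power: (1.960 + 0.842) × √(2/129) = 2.802 × 0.1245 = 0.349 (0.350 with the t distribution), against 0.31 as planned.
- Needed for 80% power at d = 0.31: 2 × 2.802² / 0.0961 = 163.4, so 164 per group.

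**Step 4: one primary, Cobb angle.** Alpha stays at one-sided 0.05, n at 129 per group and power at 80.1%. Nothing in the sample size has to change.

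**The case against.** The strongest reply is that the conflict is one of labels, and that the rest of the protocol shows what was meant. The sample-size section names a pilot effect size for Cobb angle only (0.32) and sets it against secondary outcomes. On that view Cobb angle is the real primary, and any rule for multiple testing belongs in an SAP that is not shown. The first part supports the proposed fix but does not remove the contradiction: Procedures is current text and calls SRS-22 primary. The second part is fair as far as it goes. A missing testing order is not in itself a fault of the protocol. But an SAP that split alpha between two primaries would take the trial below the protocol's own 80% power, as step 3 shows.

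Several stronger readings are tempting, and the documents do not support them:

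- A reader might infer that every radiographic measure is primary. Procedures uses a plural, but two time points could explain that, and it does not say all. The radiograph paragraph lists what is measured without ranking it.
- A reader might then count four tests (18.5% if independent) or eight (33.7%). These counts need rotations, apex translation or single SRS-22 domains to be primary, which the protocol states nowhere. The four-test count also uses an SRS-22 total that the protocol does not mention.
- A reader might infer that success on any one primary is enough. No success rule is stated. If all primaries had to succeed, there would be no inflation.
- A reader might take one-sided 0.05 per outcome as stated. It is inferred by joining the one-sided P-values in Analyses to the alpha in the sample-size section.

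**Conclusion.** The point holds in this form: Objectives and Procedures contradict each other on whether SRS-22 is primary, Procedures leaves the primary curve measurement unspecified, and the sample size pays for one primary test only. These three statements rest on the text and on a reproduced figure, and need no assumption.

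The size is conditional. If either of two primaries could carry the trial at one-sided 0.05 each, the false-positive chance is 9.75% under independence and about 7.5% to 9.3% at assumed correlations of 0.8 to 0.3. If alpha is split instead, power at 0.31 is about 70% per outcome and the detectable effect rises from 0.31 to 0.35. The contradiction should be settled before the comparative analysis, whichever of these would have applied.

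**What to change.** Amend Procedures in section 2.1 to agree with Objectives and with the sample-size section: a single primary outcome, the change in Cobb angle from baseline to 6 months, read by the evaluator blind to group. List SRS-22, rotations and apex translation as secondary. If SRS-22 is to stay confirmatory, test it only once Cobb angle is significant; this fixed order costs no alpha.

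The change leaves N, alpha and power as they are, but it is more than a wording correction. Section 4.5 says enrolment is complete, so lowering the rank of a named primary needs a dated amendment, made before any comparative results of the main trial are seen. The 25 per group from the pilot are counted in the 129 and their Cobb effect size is already reported, so the amendment should say what was known when it was written.

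The cost is that SRS-22 alone could no longer carry a positive trial. Keeping two co-equal primaries with an equal alpha split would instead need 164 per group for 80% power at 0.31, which is no ready option with enrolment closed.

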#### Schroth exercises:

Patients for which the SRS guidelines would recommend observation as standard of care will do exercises alone. Patients for which the SRS guidelines would recommend bracing will do exercises in addition to being prescribed a brace.

*Private sessions-* During the first 2 weeks, patients will attend 5 1-hour-long individual sessions to learn Schroth principles, exercises and correct breathing, and to confirm independent adequate performance with a checklist.

*Home exercises-* A 30-min. daily home exercise program of 3 to 4 exercises will be adjusted during the first 6 months using an algorithm. Compliance will be monitored using a logbook for 6 months. Completion exercises during the last 12 months will also be monitored using a logbook.

*Group Sessions-* Classes increase compliance. Patients will attend weekly 1-hour-long group therapist-led exercise classes. Adequate

exercise performance will be assessed using the checklist. Pain will be monitored.

*Algorithm* – An algorithm guides exercise prescription, intensity and progression from static to dynamic execution. Prescription begins with easier exercise. If performed adequately, a more challenging exercise will be tried. If performance is inadequate, an easier exercise will be attempted. Exercises performed adequately will be prescribed.

At follow-up, if performance is adequate, dosage will increase to target intensity. Target intensity increases repetitions aimed to enhance endurance. Final tension intensity is nearly maximum isometric contraction held in corrected posture.

During the COVID-19 pandemic, the few participants still receiving exercises will be offered the choice to receive therapy in person or via videoconference. Our therapist [name] has access to a secure videoconferencing system (JaneApp) to deliver this therapy remotely. Alternatively [name] has access to a secure ZOOM space. No recording is made during the videoconferencing session.

Controls: Controls will receive the standard of care appropriate for their curves (observation or bracing prescribed as per SRS guidelines), and will complete baseline, 3 and 6 months exams. After 6 months they will cross-over to the treatment group.

